**Statistical analysis:**

1. Regression analysis of ASQ scores with BCG, prematurity and age at follow-up as independent variables.
2. Secondary outcomes subject to post-hoc Holland correction.
3. If data are not reasonably normally distributed, we will present confidence intervals obtained by bootstrapping.

**Subgroup analyses:** Premature children, sex, BCG-immunisation within two days of birth. Subgroup analyses will be conducted in case of both statistically significant and statistically insignificant primary outcome.

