# Background

As one of the most used vaccines globally, Bacillus Calmette Guérin (BCG) vaccine is administered in > 100 countries to infants at birth to decrease the incidence of severe tuberculosis. Due to the low incidence of tuberculosis in Denmark, the BCG vaccine was withdrawn from the Danish Child Immunisation Programme in 1982. Recently, studies from West Africa have shown positive non-specific effects of early BCG immunisation on childhood morbidity and mortality (1-10). The studies suggest that BCG immunisation protects against various infectious diseases, such as pneumonia, diarrhoea, meningitis and respiratory syncytial virus (7, 11). Danish children below one year of age have high morbidity, primarily from infectious diseases, and resulting increasing use of primary care services and medication (12). Our group therefore initiated a randomised trial of BCG vaccination with the overall aim to test the hypothesis that the BCG-vaccine has positive nonspecific effects in Danish children.

It may be hypothesised that if BCG immunisation at birth results in a lower burden of disease from infections and less use of medicines, BCG immunised children may have better psychomotor development. To our knowledge it has not previously been addressed whether BCG immunisation at birth affects development. In theory, BCG immunisation at birth may also result in a low grade inflammation that may affect the brain negatively, so assessing this outcome will also address an important safety issue. The overall hypothesis of this sub-study is a non-inferiority of BCG-immunised children relating to development. Assessment of development of preterm infants is already part of the Calmette study protocol.

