### Exclusion

Infants born before gestational age 32 weeks and/or birth weight < 1000g, infants with known congenital disease, anomaly or malformation, immune deficiency and HIV, will be excluded. Non-Danish speaking parents will be excluded.

*Intervention*

Children born to mothers, who have accepted to participate, will be randomised to either intervention group or to the control group at birth. Block-randomisation stratified by gestational age (≥ 37 weeks of gestation vs. < 37 weeks of gestation) will be performed electronically just before vaccination by the overall study electronic case report system (e-crf).

Vaccination

Children randomised to the BCG vaccination group will receive an intradermal BCG vaccine (Statens Serum Institute “BCG vaccine”) in the standard dose 0.05 ml in the upper, lateral part of the shoulder of the child by specially trained midwives.

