## Sub-study outcome

Ages and Stages Questionnaire (agesandstages.com): A validated, parent reported questionnaire concerning development in five domains: Communication, gross motor, fine motor, problem solving and social development. The questionnaire results in a combined score (0 - 300) that assesses the overall psychomotor development of the child. The questionnaire will be distributed to all parents of 13 months old children born at term (Appendix 1). Parents will automatically receive an email asking whether they would like to participate in this sub-study when the child is approximately 12.5 months old. The email will contain a link that directs to a web based version of ASQ and parents type the information directly into the electronic case report form.

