## Adjustment

As the randomisation is stratified for gestational age all the statistical analyses will adjust for this factor. All main results will be presented overall and separately for girls and boys since a strong sex-differential effect of vaccines on mortality and hospitalisations has previously been found

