**Potential effect modifiers that can be considered in subgroup analyses:**

- Maternal age
- Maternal education
- Ethnicity (Danish/non-Danish)
- Parental smoking (yes/no)
- BCG with scar, BCG without scar, and control group.
- Parental atopy (eczema, asthma, allergic rhinoconjunctivitis)
- Maternal BCG (yes/no)
- Smoking during pregnancy (yes/no)
- Mode of delivery (Vaginal/Caesarean section)
- Antibiotics given to the mother during labour (yes/no)
- Birth weight (continuous)
- Breastfeeding (exclusively breast fed at three months of age (yes/no)).
- Vaccination history (vaccination before examination at 3 and 13 months)
- Batch no. (1/2)
- Infanrix Hexa (yes/no)
- Pets (yes/no)
- Siblings (yes/no)
- Day care (yes/no)

These other modifiers will possibly be explored. Data will be available on request. If very influential modifiers are found in the main study, these will be examined post-hoc.

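### As stated, the primary regression has no effective baseline adjustment if only term children are analysed; reconcile the population and pre-specify a few prognostic covariates

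*Protocol*

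**What the plan says.** Under Statistics, the Statistical analysis list gives the model as "Regression analysis of ASQ scores with BCG, prematurity and age at follow-up as independent variables". The Adjustment section explains the prematurity term: "As the randomisation is stratified for gestational age all the statistical analyses will adjust for this factor". The factor has two levels, as the Intervention paragraph under Exclusion shows: "Block-randomisation stratified by gestational age (≥ 37 weeks of gestation vs. < 37 weeks of gestation".

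Three places point to a term-only population:

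- Sub-study outcome: "The questionnaire will be distributed to all parents of 13 months old children born at term".
- Background: "Assessment of development of preterm infants is already part of the Calmette study protocol".
- Sample size considerations: the calculation uses 2,000 mature children per group, after noting that about 300 of the 4,300 will be preterm.

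One place points the other way. The subgroup line under Statistical analysis reads "Premature children, sex, BCG-immunisation within two days of birth".

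The other baseline variables have different uses. Sex is used for separate presentation of main results and as a subgroup. "Maternal education" and birth weight (as a continuous variable) are among the potential effect modifiers that may be explored. None of the three is a covariate in the stated model.

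**The concern.** A covariate with a single value cannot be estimated and explains no variance. If only term children are analysed, the model reduces to allocated arm plus age at follow-up. Age at follow-up records when the questionnaire was completed; it is not a characteristic of the child at randomisation. The primary comparison would then have no baseline adjustment, although the protocol's stated intention is to adjust.

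Sex, birth weight and maternal education are fixed before randomisation at birth and are plausible predictors of a developmental score. In a linear model, adjusting for such variables reduces residual variance and narrows the confidence interval. That interval matters here because the sub-study is framed as non-inferiority. What is at stake is some precision, together with clarity about which children the primary result describes.

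**Working it through.** **1. Is prematurity constant?** Sub-study outcome, Background and Sample size considerations all describe term children. On that reading the prematurity column is zero for every child. A design matrix with intercept, arm, prematurity (all zero) and age has four columns but rank 3. The term drops out, and the arm estimate is the same with or without it. On the subgroup line's reading, some preterm children are analysed; the column then varies and is the stratification factor. The protocol does not say which reading governs the primary analysis.

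**2. Inputs.** From Sample size considerations: 2,000 per arm, SD 40, difference 5 points, α 0.05 (sidedness not stated; two-sided used here). From Sensitivity analyses: data expected on about 85% of children, so 0.85 × 2,000 = 1,700 per arm. Assumed: the added covariates explain a share R² of the variance, with 2–10% as the working range. SD 40 is taken as the SD before they are added.

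**3. Formulas.**

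- SE = 40 × √(1 − R²) × √(2/n)
- 95% CI half-width = 1.96 × SE
- Power = Φ(5/SE − 1.96)
- Equivalent n per arm = n/(1 − R²)

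**4. The protocol's own figure.** With n = 2,000 and R² = 0, SE = 40 × √(2/2,000) = 1.265 and power = Φ(3.953 − 1.96) = 97.7%. With the rounded effect size of 0.12 (4.8 points), power is 96.7%. Both agree with the stated figure of about 97%, which therefore needs no covariates.

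**5. With the added covariates, at 1,700 per arm.**

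| Assumed R² | SE | 95% CI half-width | Power for 5 points | Equivalent n per arm |
|---|---|---|---|---|
| 0 | 1.372 | 2.69 | 95.4% | 1,700 |
| 0.02 | 1.358 | 2.66 | 95.7% | 1,735 |
| 0.05 | 1.337 | 2.62 | 96.2% | 1,789 |
| 0.10 | 1.302 | 2.55 | 97.0% | 1,889 |

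The interval narrows by 1 − √0.98 = 1% to 1 − √0.90 = 5%. This equals 35 to 189 more responders per arm.

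**6. With all 2,000 per arm.** Over the same R² range, the half-width goes from 2.48 to 2.45–2.35 points and power from 97.7% to 97.9–98.6%.

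**7. A more generous assumption.** At R² = 0.20 and 1,700 per arm, the half-width is 2.41 points and power is 98.3%.

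**The case against.** The strongest reply is that this is a preference and not an error. In a randomised comparison of means, omitting prognostic covariates leaves the arm effect unbiased. The model follows the protocol's own rule of adjusting for the stratification factor, and the outcome is defined as age-adjusted. A fuller covariate set could stand in a statistical analysis plan that is not shown. The gain is 0.03 to 0.14 points of half-width in a study that already has about 95% power. All of this stands, and it limits the point to an improvement. It does not remove the point, because the protocol itself writes out the model, and the prematurity term and the population text do not fit together.

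A reader might also infer more than the documents support:

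- **That prematurity is certainly a constant.** It is so only on the term-only reading, which the premature subgroup contradicts.
- **That non-response biases the result and adjustment would cure it.** About 15% of data are expected to be missing, but nothing says that this depends on maternal education or differs by arm. If response depended on a baseline variable equally in both arms, the arm contrast would be unbiased unless that variable also modified the effect. Multiple imputation of completely missing scores is already planned as a sensitivity analysis.
- **That gestational age in weeks is already held.** The protocol shows only the 37-week stratum and the 32-week exclusion limit. Recording in weeks is a reasonable inference, not a stated fact.
- **That the non-inferiority conclusion depends on these covariates.** The protocol states no margin (the 5 points are a difference to detect), so no such effect can be shown.

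**Conclusion.** The point holds as a free improvement. The textual fault is firm but minor: the model adjusts for prematurity and the plan has a premature subgroup, while the questionnaire and sample size are confined to term children. If the term-only reading governs, the stated model has no effective baseline adjustment.

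The cost is precision only. With R² between 2% and 10%, adding covariates narrows the interval by 1–5% and raises power by 0.3 to 1.6 percentage points at 1,700 per arm. This rests on the assumed R², on SD 40, and on 85% response applying equally to both arms of 2,000. The protocol's power statement reproduces and is not in question.

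**What to change.** 1. State whether preterm children are in the primary analysis, and bring Background, Sub-study outcome, Sample size considerations and the subgroup line into agreement.
2. If they are included, keep the two-level prematurity term, since the Adjustment section commits to it. If they are not, drop it as redundant and say so.
3. Pre-specify sex, birth weight and maternal education as covariates in the primary model, beside allocated arm and age at questionnaire. Add gestational age in weeks if it is recorded; where preterm children are included, this supplements the stratification term and does not replace it.
4. Use the same variables in the multiple-imputation model.
5. Report the model as the protocol now states it as a sensitivity analysis.

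The cost is a change of wording. Sex, birth weight and maternal education are already named for other analyses, so no new data collection is implied for them; for gestational age in weeks, recording must first be confirmed. Fixing the list in advance also keeps the covariates from being chosen later from the long list of possible effect modifiers.

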# Summary

Recent studies from Africa have shown that Bacillus Calmette-Guérin (BCG) vaccination is associated not only with specific protection against tuberculosis, but also with so-called non-specific beneficial effects. We recently initiated a large randomised trial of BCG vaccination in Denmark to test the hypothesis that BCG vaccination at birth has beneficial nonspecific effects on child health in Denmark. No less than 4,300 infants born at Rigshospitalet, Hvidovre Hospital and Kolding Sygehus will be randomised to BCG at birth or no vaccine (control group). Follow-up will continue until the children are 13 months of age (22 months for premature infants born before 37 weeks of gestation). Data will be collected using structured telephone interviews and clinical examinations at age 3 and 13 months.

This is a non-inferiority sub-study aiming to examine whether BCG immunisation at birth affects child development.

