# Sample size considerations

The overall trial

The main trial includes 4300 children to be able to detect a 20% reduction in infant hospitalisation with 90% power and α = 0.05.

Sub-study

The entire Calmette-cohort will comprise 4300 children. Of these approximately 300 will be preterm (< 37 GA). Based on a sample size of 2000 mature children in each group, an α = 0.05, a mean ASQ score of 200 with a standard deviation (SD) of 40 this study will have a power of approximately 97% to detect a 5 points difference (effect size 0.12) between mean scores in BCG vaccinated children compared to unvaccinated children. When used for screening purposes, an ASQ score of ≥1.5 SD (approximately 60 points at age 13 months) below the mean is considered indication of developmental delay (13). The high power of this sub-study will allow meaningful exploratory subgroup analyses.

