**Sensitivity analyses:**

We expect to have data on approx. 85% of enrolled children. Some of these data may be incomplete. The ASQ manual suggests that partially completed scores can be used to impute the total score. The equation is: total ASQ score = sum of ASQ sub-scores / (300 - 10 * no. of missing)*300. In case of questionnaires less than 66% complete, they will count as missing. Sensitivity analyses using the simple imputation-data will be conducted.

Completely missing scores will be imputed using multiple imputations. Questionnaires less than 66% filled will be set to missing and then imputed.

Excluding children that did not follow the allocation.

**Exploratory outcomes:** Correlation of age-adjusted ASQ sum-score with sum of parent reported illness. Exploratory analyses will be presented with crude p-values not corrected for multiple comparisons.

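### The two-day subgroup is defined by vaccination timing, which only the BCG arm has; taken literally it restricts one arm and is not a randomised comparison

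*Protocol*

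**What the plan says.** The Statistics section of the protocol (Statistical analysis) lists the subgroups as "Premature children, sex, BCG-immunisation within two days of birth". It adds that subgroup analyses will be run whether or not the primary outcome is significant. It names no comparator for the third subgroup and no way of placing control children in or out of it.

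Other parts of the protocol bear on this:

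- **Control arm (Summary).** Infants "will be randomised to BCG at birth or no vaccine (control group"). No placebo is described.
- **Time of randomisation (Intervention, under Exclusion).** Children "will be randomised to either intervention group or to the control group at birth", and the block randomisation "will be performed electronically just before vaccination by the overall study electronic case report system (e-crf").
- **Adherence (Sensitivity analyses).** One sensitivity analysis is "Excluding children that did not follow the allocation", so the authors allow for children who do not receive what they were allocated.
- **Another variable that depends on vaccination (Potential effect modifiers).** Here the groups are spelled out: "BCG with scar, BCG without scar, and control group".
- **Status (Sample size considerations).** Subgroup analyses are described as exploratory.

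**The concern.** A control child has no vaccination date and so can neither meet nor fail the two-day criterion. As a filter, it acts on the BCG arm and leaves the control arm whole.

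Children who enter the trial after day two may differ from those who enter at once, for reasons unrelated to BCG. Randomisation puts such children in both arms in equal proportion. The filter then removes them from one arm. BCG-arm children vaccinated late or never are removed as well. The remaining contrast mixes any effect of BCG with the difference between early and late children.

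The Background section presents possible harm to development as a safety question, and the overall hypothesis is non-inferiority. A result for children vaccinated early is likely to be read as evidence on that question. A contrast that can show a difference when BCG does nothing, or hide one when it does something, is a poor basis for that reading.

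**Working it through.** **The plan's own figure.** The sample size section reads "Based on a sample size of 2000 mature children in each group, an α = 0.05, a mean ASQ score of 200 with a standard deviation" of 40, and claims "power of approximately 97% to detect a 5 points difference (effect size 0.12"). The standard error is 40 × √(2/2000) = 1.265, and 5/1.265 = 3.95. Two-sided power is Φ(3.95 − 1.96) = Φ(1.99) = 0.977, which agrees. (Sidedness is not stated; one-sided power would be 0.990.) This figure is for the whole term sample. No figure is attached to the two-day subgroup.

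**Inputs for the subgroup.**

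- From the protocol: SD 40, and 2000 per group with data on about 85%, so 0.85 × 2000 = 1700 per arm.
- Assumed, because the protocol gives neither: f, the share of children who are late (after day two), equal in the two arms; and g, the mean ASQ score of early children minus that of late children, for reasons other than BCG.

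**Bias when BCG has no effect.** Let early children have mean m.

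- Early BCG children: m
- All controls: (1 − f) × m + f × (m − g) = m − f × g
- Difference: f × g

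The sign of the bias is the sign of g. The table takes g as positive; a negative g reverses the bias and leaves the type I error unchanged.

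**Type I error.** With SE = 40 × √(1/(1700(1 − f)) + 1/1700), the two-sided error at nominal 0.05 is 1 − Φ(1.96 − f·g/SE) + Φ(−1.96 − f·g/SE). Cells show bias in points, with type I error in brackets.

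| f (late) | SE | g = 2 | g = 5 | g = 10 |
|---|---|---|---|---|
| 5% | 1.39 | 0.1 (0.051) | 0.25 (0.054) | 0.5 (0.065) |
| 10% | 1.41 | 0.2 (0.052) | 0.5 (0.065) | 1.0 (0.109) |
| 20% | 1.46 | 0.4 (0.059) | 1.0 (0.106) | 2.0 (0.279) |
| 30% | 1.51 | 0.6 (0.068) | 1.5 (0.168) | 3.0 (0.510) |
| 50% | 1.68 | 1.0 (0.091) | 2.5 (0.319) | 5.0 (0.845) |

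For scale, g = 10 is 10/40 = 0.25 SD, twice the 5-point planning difference. The right-hand column is therefore a severe case.

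**With both arms restricted by age at randomisation.** Early children are compared with early children, and the bias is zero by randomisation. Power for 5 points among early children, with 1700(1 − f) per arm, is 0.944, 0.933, 0.903, 0.862 and 0.731 for the five values of f.

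**The case against.** The strongest reply is that the protocol gives only a short label in a list. It does not say that early-vaccinated children will be compared with all controls. Where the authors want the control group as comparator, as with scar status, they say so. An analysis plan that is not shown could match controls by age at randomisation. This stands as far as it goes: a reader might infer that the unmatched contrast is planned, but the protocol does not state it. It does not rescue the definition. The variable named is vaccine receipt, and a later document could give a randomised comparison only by replacing it. The scar example points, if anything, to vaccinated subsets being set against the whole control group.

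A reader might also infer that the main problem is children delayed after allocation by illness or hesitation. The protocol does not support that as the main route. Randomisation takes place just before vaccination, so early randomisation and early vaccination should nearly coincide. Most of the bias would come from late-randomised children left among the controls, with a smaller part from BCG-arm children vaccinated late or never.

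The size may also be slight. Children with known congenital disease, malformation or immune deficiency are excluded, and the questionnaire goes to parents of children born at term. Both may narrow the gap between early and late children. If few children are randomised after day two, the bias is a fraction of a point. This stands.

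**Conclusion.** The subgroup is wrong as written, and the defect is confined to an exploratory analysis. The stated variable exists in one arm only, arises after randomisation and comes with no rule for controls, so it cannot by itself give a randomised comparison.

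The size rests on two assumed quantities. Reference points for the bias are 0.1 points (f = 5%, g = 2), 0.5 (f = 10%, g = 5) and 2 (f = 20%, g = 10). These are 2%, 10% and 40% of the 5-point planning difference. They assume the all-controls comparator and equal late shares in the two arms.

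Two stronger readings go beyond the documents. One is that the contrast would favour BCG: that needs late children to score lower, and nothing in the protocol shows this. The other is that late-vaccinated children would appear harmed by BCG: that needs a comparison of late BCG children with all controls, which the protocol does not name. The primary outcome, the main regression and the 97% power do not depend on this subgroup.

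**What to change.** Replace the third subgroup with *randomised within two days of birth (yes/no)*, applied to both arms. Analyse by allocated arm and add a BCG × age-at-randomisation interaction to the planned regression. Use the randomisation time from the e-CRF. Electronic randomisation implies that a time is recorded, but the protocol does not say so, so confirm it.

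The change costs one line of wording and touches no clinical procedure. It has two downsides:

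- The question shifts slightly, from actual age at vaccination to age at randomisation. Since the protocol places the two close together, little should be lost.
- The interaction will be imprecise if few children are late. Its standard error is 40 × √(2/(1700(1 − f)) + 2/(1700f)). At f = 10% this is 40 × √(2/1530 + 2/170) = 4.57 points, and at f = 20% it is 40 × √(2/1360 + 2/340) = 3.43 points. Report it with its confidence interval, and do not read a non-significant result as evidence that timing makes no difference.
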